**Figure 4 nutrients-07-05226-f004:**
[figure not shown]
Example of using the mobile food record (mFR) to assess individually packaged foods. (**a**) Before eating image; (**b**) After eating image.

#### 2.3.3. Fruit and Vegetables

A diet consistent with the Australian Dietary Guidelines can help maintain a healthy weight and assist in the prevention of chronic diseases, such as cardiovascular disease, type 2 diabetes and some cancers [7,8,20,51]. Previous studies have found Australian adults eat less than the recommended daily serves of fruit and vegetables [52], supported by the most recent Australian Health Survey which found only three per cent of young adults meet the recommended two 150 gram serves of fruit and five 75 gram serves of vegetables per day, compared to 9.6% of older adults [53]. The reasons why people are not eating enough fruit and vegetables are complex but household income and the expense of fruit and vegetables have been shown to be significant factors [54,55]. In recent years, changes in climate have influenced the availability and affordability of some fresh fruits and vegetables in Australia [22,56]. The cost of fresh fruit and vegetables in Australia appears to be increasing at a higher rate than other food categories, evidenced by an 18.8% increase in the cost of fresh fruit and 10.7% increase in fresh vegetables in Western Australia since 2010 [57].

Diets high in fruit and vegetables have a lesser impact on the environment than those high in processed foods or animal-based foods [3,15]. Although the consumption of a diet that consists of mostly fresh fruits and vegetables is encouraged [7], it has been suggested that additional considerations need to be included, for example, produce grown locally and in season. This is because fruits and vegetables grown locally or in season are less likely to require a climate controlled environment and typically undergo less processing, packaging, transportation and storage [58,59]. However, other studies have suggested the benefits of consuming locally grown seasonal produce is not the determining factor of environmental impact because food production has more impact on the environment than transportation [12,60,61]. A recent study by Drewnowski *et al.* [11] assessed the relationship between nutrient and energy density and carbon footprint, and found that processed and frozen fruit and vegetables had a low carbon footprint when considered as per 100 grams in comparison to meat and dairy products. But when looking at energy density per 100 kcal, the carbon footprint of frozen and processed fruit and vegetables increased dramatically [11]. This study pointed out that carbon footprint is only one of many metrics to assess the environmental impact of food. Overall, it is widely accepted that some fruits and vegetables are more emissions-intensive than others depending on several factors, including country of origin, the need for protected conditions, storage and cooking.

Choosing seasonal local fruits and vegetables requires specific knowledge of where food was grown. This information is not always evident or available to consumers [7] particularly when meals are prepared by others (e.g., meals eaten at a restaurant). Studies have shown people are prepared to buy local produce, although factors such as convenience, price, accessibility and perceived quality also determine purchasing habits [50,62].

Using the protocol outlined in this paper, the intake of fruit and vegetables will be analysed from each eating image pair and classified according to the Australian Dietary Guidelines serve sizes (1 serve of vegetables = 75 grams, ½ cup cooked vegetables or 1 cup of salad vegetables, and 1 serve of fruit = 150 grams, 1 medium piece or 2 small pieces of fruit). A Microsoft Access database tool will be created to record the estimated serve size and type of fruit and vegetable consumed separately. This feature will allow for further assessment of the environmental impact of different varieties. As the time and date stamp is available from images collected with the mFR, the date fruits and vegetables were consumed can be recorded and merged within the database containing information on when each fruit and vegetable is in season. For example, in Western Australia bananas are in season in summer and autumn, meaning if someone consumed a banana between 1st December and the 30th May then the banana will be recorded as “eaten in season”. For this study, seasonal fruits and vegetables will be classified according to the Western Australia (WA) Seasonal Fruit and Vegetable Calendar [63].

Dietary assessment of seasonal and local fruit and vegetable intake poses significant challenges including: the additional burden of recording “place of origin” at time of purchase; prepared food not carrying this information (e.g., buying a salad at a café): and the sale of fruits and vegetables all year around, regardless of seasonality. A limitation of assessing the intake of seasonal fruit and vegetable intake is that there is no way of determining the origin of fresh produce, for example a banana from Queensland could be eaten in Western Australia, 4341 kilometres away by road (the main transportation method used). However, consuming seasonally available produce, regardless of origin, is likely to reflect an aspect of a healthy and sustainable diet. There is currently limited data on the intake of seasonal fruits and vegetables by adults in Australia. As less than 7% of Australians consume the recommended daily serves of vegetables and less than half consume the recommended two serves of fruit [64], increasing intake alone, regardless of seasonality, would result in health benefits.

An example of fruit to be consumed can be seen in the mFR image (as it appears using the web application hosted on a secure server) in Figure 5. Using this example containing the date of the image, one serve of fruit (e.g., one medium banana) would be entered in the database and because this eating occasion took place in September in Western Australia, this piece of fruit would be considered eaten “out of season”.

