## 2. Experimental Section

### 2.1. Study Participants

The study sample to be used for developing the proposed methods will consist of 247 adults aged from 18 to 30 years, comprising of 162 (66%) women and 85 (34%) men previously recruited for another study, the Connecting Healthy and Technology study, referred to as CHAT [26]. Recruitment involved sending letters of invitation to 15,000 residents from 57 suburbs (using the Socio-Economic Indexes for Areas) in the Perth Metropolitan Area from the Federal Electoral Roll, a compulsory enrolment system for Australians aged over 18 years. Participants were screened either online, using a survey website, or on the telephone to ensure the inclusion criteria were satisfied (aged between 18 and 30 years and owned a mobile phone). For the original study, potential participants were excluded if they were: (a) unable to attend on four occasions to complete the 6-month randomised controlled trial; (b) studied nutrition; (c) took part in extreme forms of exercise; (d) followed a restrictive diet; or (e) pregnant or breastfeeding. The CHAT study was conducted between July 2012 and June 2013.

The Connecting Health and Technology study was registered on the Australian and New Zealand Clinical Trials Registry (ACTRN12612000250831) and approved by the Curtin University Human Resources Ethics Committee (HR181/2011) and the Western Australian Department of Human Research Ethics Committee (#2011/90).

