For the development of the proposed methodology, participants completed an mFR at baseline (*n =* 247) and repeated this six months later (*n =* 220). A secondary analysis by the Accredited Practising Dietitian who was involved in the original analysis of all food images collected during the CHAT study will take place. A purpose built Microsoft Access database will be developed to assess the contents of images, and the review of each image pair (including a before and after eating image). A minimum of one image pair per day will be required to be considered a valid day. Five indicators of a healthy and sustainable diet will be assessed using the images captured using the mFR. An objective of this study is to determine whether the five selected dietary behaviours can be assessed from image-based food records without interaction with participants. This is therefore a “proof of concept” approach to developing the Index before replication in possible future interventions. A flowchart outlining the design of the proposed study can be seen in Figure 2.

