### 2.3. Assessment of Healthy and Sustainable Dietary Behaviours

For the development of a *Healthy and Sustainable Diet Index*, dietary behaviours were identified from evidence of their supportive or unsupportive role within a healthy and/or a sustainable diet and the inclusion of details that can be assessed using images. Descriptions of each component’s role within the context of a healthy and sustainable diet are outlined below. The five indicators to be assessed using the mFR application include: the intake of ultra-processed EDNP foods and beverages, individually packaged foods and beverages, fruit and vegetables (including seasonality), dairy, eggs and meat portions, and plate waste. These dietary behaviours will be assessed using the following proposed methodologies.

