Each component incorporated into the *Healthy and Sustainable Diet Index*, will be given a weighting used to calculate a final score measuring adherence to a healthy and sustainable diet. For example, typically indices have a maximum score of 100, with a higher score indicating greater adherence to the preferred dietary pattern [23]. Individual components will be given a weighting to reflect consistency with the recommended dietary and sustainable eating outcomes, for example, fruit and vegetable intake may be given a higher weighting as it contributes to both healthy and sustainable eating.

The theoretically driven *Healthy and Sustainable Diet Index* will be internally validated for reliability, content validity and construct validity using 4-days image-based food records collected during a 6-month randomised controlled trial. The baseline data collected during the CHAT study (*n =* 247) will be randomised into thirds using age- and sex-stratified random sample techniques. Two-thirds of the sample will be randomly selected as the derivation cohort and the image-based mFRs of those selected will be used to develop the *Healthy and Sustainable Diet Index* using regression techniques. The remaining one-third of the sample will be used as the validation cohort for the *Healthy and Sustainable Diet Index*. This Index will also be used in the assessment of food images from the 6-month follow up (*n =* 220), and the results compared with baseline.

To assess content validity, components of the *Healthy and Sustainable Diet*
*Index* will be assessed against the Australian Dietary Guidelines [7]. Construct validity will quantitatively assess how well the Index measures conformance to a healthy and sustainable diet.

To determine a total score using the *Healthy and Sustainable Diet Index*, density scores for each component will be calculated. Internal consistency, one form of reliability, will be assessed using Cronbach’s coefficient α. This test has previously been used in the evaluation of the Healthy Eating Index [70] to examine the degree of association between components, to determine if a diet only has one dimension. The relationship between the components of the *Healthy and Sustainable Diet Index* will be assessed using Pearson correlations coefficient. Principle component analysis will be used to assess if there are independent components of the Index. This will measure if there are any significant independent predictors of an overall score.

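### Seasonality is scored by consumption date and the two records are six months apart, so the comparison of the 6-month Index with baseline can contain a calendar effect.

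*Protocol article*

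**What the plan says.** All references are to the protocol article.

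- **Scoring rule (section 2.3.3).** The date stamp of the image is merged with a table of seasons, and "seasonal fruits and vegetables will be classified according to the Western Australia (WA) Seasonal Fruit and Vegetable Calendar". In the worked example, "if someone consumed a banana between 1st December and the 30th May then the banana will be recorded as" in season. A second example classes a banana as out of season "because this eating occasion took place in September in Western Australia".
- **Place in the Index (section 2.3).** Seasonality belongs to one of the five indicators, listed as "fruit and vegetables (including seasonality), dairy, eggs and meat portions, and plate waste". Section 2.4 also lists it among the outcome variables.
- **Timing (sections 2.1 and 2.2).** "The CHAT study was conducted between July 2012 and June 2013". Participants completed a record at baseline (n = 247) "and repeated this six months later" (n = 220).
- **Planned use (section 2.5).** "This Index will also be used in the assessment of food images from the 6-month follow up", "and the results compared with baseline".
- **Weight (section 2.5).** Components that images cannot measure accurately, with seasonality as the example, will not be weighted highly. No number is set.

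No section says how the comparison with baseline will deal with season. Section 2.3.3 discusses difficulties in assessing seasonal and local produce, such as unknown origin and year-round sale, but not the six-month gap.

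**The concern.** For any item, the score depends on when it was eaten as well as on what was chosen. Two records six months apart sit on opposite sides of the year. A person who eats the same seasonal item at both records can move from out of season to in season, or the reverse, with no change in food choice. The comparison with baseline is within person and has no concurrent reference, so nothing in it removes such a shift.

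At stake is how the 6-month result is read. A rise or fall in the Index could be reported as a change in healthy and sustainable eating when part of it comes from the months in which the two records were taken.

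**Working it through.** **Inputs**

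- Banana window: 1 December to 30 May (section 2.3.3).
- Interval between records: six months (section 2.2).
- Study dates: July 2012 to June 2013 (section 2.1).
- Assumption: these dates run from first baseline to last follow-up. The article does not say so outright.

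**1. Reproduce the article's own example.** September lies outside 1 December to 30 May, so the rule gives out of season. This agrees with the Figure 5 example in section 2.3.3.

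**2. Place the visits.** If the last follow-up is in June 2013 and the interval is six months, the last baseline is in December 2012. Baselines then fall in July to December 2012 and follow-ups in January to June 2013.

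**3. Share of days in season, banana**

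- July to December 2012: only December counts. 31 / 184 = 16.8%.
- January to June 2013: 1 January to 30 May is 31 + 28 + 31 + 30 + 30 = 150 days. 150 / 181 = 82.9%.

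**4. Pair each baseline date from 1 July to 31 December 2012 with its follow-up date**

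| Interval | Baseline dates | Out to in | In to out | Unchanged |
|---|---|---|---|---|
| 182 days | 184 | 152 | 31 | 1 |
| Six calendar months | 184 | 153 | 31 | 0 |

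At 182 days, 183 of 184 dates change class. For this fruit the flips are lopsided: 153 / 184 = 83% go from out to in and 31 / 184 = 17% from in to out. They would not cancel if recruitment were spread evenly over those months.

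**5. Vary the interval, keeping both records inside the study dates**

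| Interval (days) | Dates changing class | Share |
|---|---|---|
| 154 | 184 of 211 | 87.2% |
| 168 | 184 of 197 | 93.4% |
| 182 | 182 of 183 | 99.5% |
| 196 | 154 of 169 | 91.1% |
| 210 | 126 of 155 | 81.3% |

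The result does not hinge on an exact interval.

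**6. Vary the produce.** The calendar is not shown, so these season lengths are assumed. The share of baseline months in which an item changes class after six months is:

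- one continuous six-month season: 100%
- one continuous three- or nine-month season: 50%
- year-round: 0%
- summer plus winter: 0%

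**7. Carry it to the Index.** Shift in Index points = points for seasonality × net share of the seasonality score that flips. Neither factor is in the article, and a maximum of 100 is mentioned only as typical of indices. Purely as illustration on a 100-point scale, with net flips of 25% to 100%:

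- 2 points: 0.5 to 2
- 5 points: 1.25 to 5
- 10 points: 2.5 to 10

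The shift is zero if seasonality earns no points or if the flips cancel.

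**The case against.** The strongest reply is that this is the construct, not an artefact. Section 2.4 defines the outcome as whether produce was in season when and where it was eaten. Someone who eats bananas in September and again in March has eaten out of season once and in season once, and the score records that. This stands as a defence of the score at a single record. It does not settle how a change between records is read, because the change then mixes what people chose with the month in which they were asked.

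Several stronger readings are tempting, and the article does not support them.

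- **Any unchanged diet will show a changed Index.** The banana is one illustration. Other items may flip the other way or not at all, so the net sign for a mixed diet is unknown.
- **Season is fully confounded with visit.** July to December takes in winter, spring and December; January to June takes in summer, autumn and June. The 17% and 83% show that both states occur at both visits. What nearly coincides is calendar month and visit.
- **A 6-month reliability coefficient is spoiled.** The only reliability statistic named in section 2.5 is Cronbach's α, which measures internal consistency. The Discussion mentions a longitudinal sample and reliability, but no test-retest coefficient is specified.
- **The derivation and validation cohorts are biased.** Both come from a random split of baseline data. Recruitment month adds variation between people there, not a systematic difference between cohorts.

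It is also fair that the weights are still to be developed, that a high weight is already ruled out, and that a condensed article need not carry every analysis detail. These points limit the likely size. They do not remove the effect, since the rule, the interval and the comparison are all stated and a weight that is not high is still not zero.

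**Conclusion.** The concern holds in a limited form. From the article's own rule and interval, an item with a season of about six months changes class between the two records on nearly every baseline date: 183 of 184 for a banana at 182 days, and 81% to 99.5% of dates at intervals of 154 to 210 days. The planned comparison of the 6-month Index with baseline can therefore contain a calendar effect.

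The half-year counts rest on reading the stated study dates as first baseline to last follow-up. The size and direction of the effect on the whole Index cannot be derived, and it may be small. The point bears on how one planned comparison is interpreted. It does not undermine the Index or its derivation from baseline data.

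A separate slip needs only a minor correction: the example describes the banana season as summer and autumn, which ends on 31 May, but gives 30 May.

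**What to change.** In section 2.5, state two things:

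1. The change from baseline to 6 months will be reported for the Index without the seasonality sub-score, alongside the full Index. Fruit and vegetable serves stay in both.
2. A change that appears only in the full Index will not be read as a change in behaviour.

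A seasonality score taken relative to what is in season that month could be added as a sensitivity analysis. It measures a somewhat different thing, so it should not replace the planned score. Adjustment for calendar month should not be relied on: month and visit are nearly collinear here, so a model could not separate them.

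In section 2.3.3, end the banana window on 31 May so that it matches the stated seasons.

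The cost is one extra reported result and two sentences of text. No new data are needed.

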**Figure 5 nutrients-07-05226-f005:**
[figure not shown]
Example of using the mobile food record to assess seasonal fruit and vegetable intake.

#### 2.3.4. Dairy, Eggs and Meat Products

There is substantial evidence supporting the additional environmental impact of meat and dairy foods, compared to plant-based foods [2,14,65]. Along with a growing population and urbanisation, there is a global transition from largely plant-based diets to diets higher in EDNP foods and animal-based foods [45], increasing burden on the food system. While the consumption of dairy foods in Australia is generally below dietary recommended levels, Australians traditionally consume large volumes of meat, with the consumption of beef constituting the highest amount [15]. Meat and dairy products from ruminant cattle and sheep are some of the greatest greenhouse gas contributors in modern diets [8,9].

Previous research in the area of sustainable diets has highlighted a healthy and sustainable diet can be followed without the complete exclusion of dairy and meat [1,2,8,65], however, excessive red meat and processed meat consumption has been linked to an increased risk of colorectal cancer [7,66]. To accommodate this, the latest review of the Australian Dietary Guidelines reduced the standard serving size of lean red meat to a set 65 grams from the previous range of 65 to 100 grams of cooked meat, with a maximum of seven serves, or 455 grams, of red meat per week [7]. In Australia, only 2.1% of people avoid red meat [53]. Therefore, comparing meat intake between small, moderate and large meat consumers is relevant in assessing a healthy and sustainable diet when only a small percentage of the population are vegetarians [67].

When applying the proposed method to this component, food images will be used to estimate average daily intake of milk, cheese and yoghurt, eggs and meat products (including red meat, poultry and fish). The volume of specific types of dairy, eggs and meat products (e.g., beef mince) will be recorded as an approximate gram or millilitre weight and compared to the Australian Dietary Guidelines recommendations [7]. Meat consumed in other food products assessed using this method, such as a beef patty in a commercial burger, will be counted as ultra-processed EDNP food serves and also meat serves.

#### 2.3.5. Food Waste

Australians throw away $5.3 billion Australian dollars (AUD) worth of food each year. This includes fresh food (AUD $2.9 billion), frozen food (AUD $241 million), take-away food (AUD $630 million), unfinished drinks (AUD $596 million) and leftover food (AUD $876 million) [68]. Young adults waste more food than older adults with 38% of 18–24 year olds wasting more than AUD $30 on fresh produce per fortnight, compared to only seven percent of older adults [68]. Reducing food waste from production to consumption will decrease burden on the food system, in turn benefiting the environment [69]. Discrepancies were detected in an Australian study comparing reported household fresh food waste (AUD $4.6 million) and actual fresh food waste (AUD $8 billion), collected during a household garbage bin audit [68]. The methods proposed here will accurately capture an important element of food waste, consumer plate waste, through the use of before and after eating food images, to support an area of research with a lack of sufficient data [69].

Image pairs allow for the accurate assessment of plate waste due to the presence of before eating and after eating images. Plate waste will be estimated as a percentage of food or beverage not consumed in the after eating image. Food waste in each image will also be classified as compostable (e.g., fruit, vegetables, egg shells), not compostable (e.g., meat and dairy) or unable to determine.

An example of red meat intake and food waste can be seen in Figure 6. Using the described protocol, this eating occasion will be assessed as four serves of roast beef, and having 30% edible plate waste. Note, one serve of cooked beef is 65 grams [7].

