### 2.2. Study Design

During the Connecting Health and Technology study, participants completed four day mFRs using the CHAT application at baseline and at the end of the 6-month randomised controlled trial. During both visits height and weight data were collected. Participants were asked to capture before and after images of all eating occasions using a mobile device (iPod Touch) provided by the research team. On the initial visit participants were taught how to use the specifically designed dietary assessment method, the CHAT application, uploaded onto the iPod Touch (iOS6). Participants were asked to place a small fiducial marker in the bottom left hand corner of every image to assist in portion size and colour estimation [38]. Details of the mFR CHAT application have been previously described by Kerr *et al.* [39].

Participants were asked to take images over four consecutive days, from Wednesday to Saturday. On completion of the food record, participant’s clarified the contents of images with an Accredited Practising Dietitian, and verified plate waste or if the leftover food or beverage was consumed at a later stage. Each image obtained during the CHAT study contains metadata on the time, date and location it was taken, allowing for the assessment of whether fresh produce were in season at time of consumption. The food images collected during the CHAT study will be used to validate and test the *Healthy and Sustainable Diet Index*.

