Ultra-processed foods are defined as those that require minimal, if not any, culinary preparation [41]. Previous studies have relied on household expenditure surveys and semi-quantitative food frequency questionnaires to assess the intake of ultra-processed foods [41,42,43], yet no studies have investigated the consumption of ultra-processed foods in Australia. A unique aspect of the methods to be used is that EDNP ultra-processed foods will be assessed using image-based mFRs. For inclusion in this component only ultra-processed foods and beverages categorised as energy-dense and nutrient-poor, such as cakes, crisps, commercial burgers and sugar-sweetened beverages will be used [7]. Ultra-processed EDNP foods and beverages will be assessed according to the Australian Dietary Guidelines serve sizes-one serve of EDNP food or beverage being equivalent to 600 kJ (143 kcal) [7]. Nutrient dense foods that are highly processed, such as bread, will be excluded due to associated health benefits.

An example image of ultra-processed EDNP foods collected using the mFR application can be seen in Figure 3. Using the proposed assessment protocol, this eating occasion would be recorded as 14 serves of ultra-processed EDNP foods. The two pieces of fried chicken appearing in the after eating image would not be counted as ultra-processed EDNP serves but rather non-compostable food waste.

We can appreciate all EDNP foods may not necessarily be worse for the environment than other food items, however, in regard to health consequences, these food items offer minimal, if any, nutritional benefit. In addition, the excessive intake of kilojoules above an individual’s energy requirements, from these EDNP foods and beverages, is a dietary behaviour unsupportive of health whilst creating unnecessarily burden on natural resources.

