## 3. Discussion

The proposed methodologies described in this paper aim to determine if the mobile food record can be used to accurately measure five key indicators of a healthy and sustainable diet. The availability of dietary intake data collected from 4-day mFRs during the CHAT study enables the refinement of the assessment tool and internal validation of a theoretically driven *Healthy and Sustainable Diet Index*. This Index will be tested on a duplicate sample and a longitudinal sample of adults’ 4-day image-based food records to measure content validity, construct validity and reliability.

The *Healthy and Sustainable Diet Index* will be unique in two ways; firstly it will combine the assessment of eating behaviours that influence health outcomes (e.g., EDNP foods and beverages) and dietary behaviours that significantly burden the environment (e.g., ultra-processed foods, food waste). Secondly, it will require the use of image-based food records, which will enable the accurate assessment of dietary behaviours not assessed in traditional forms of dietary assessment (e.g., individually packaged foods).

Using an mFR application to assess the five healthy and sustainable dietary behaviours described in this paper has the potential for further enhancement of the mFR applications capability as a new dietary assessment method. For example, a current fiducial marker probe exists to alert users when the fiducial marker is not located in the image, as described by Ahmad *et al.* [29]. A similar mechanism to ask the user whether food waste detected in the after image was thrown in the rubbish bin, composted, saved for consumption at a later time or other could be incorporated into the mFR application.

Currently there is limited evidence on whether Australian adults have dietary habits consistent with a sustainable diet. Without adequate evidence in this area, appropriate changes to dietary recommendations and nutrition policy are challenging. Results from the Australian Health Survey indicate most Australian’s have eating habits inconsistent with the Dietary Guidelines, contributing to the burden of diet-related diseases in this country [63]. However, to the authors’ knowledge, there is currently no dietary assessment tool or indexing system to assess and monitor whether individuals have dietary behaviours inconsistent with a sustainable diet, such as the use of individual food packaging and plate waste.

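### The plate-waste percentage in section 2.3.5 does not exclude leftovers eaten later, although the record interview in section 2.2 established which leftovers those were

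*Protocol article*

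**What the plan says.** The following parts of the protocol article bear on how plate waste is scored.

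- **Section 2.3.5 (Food Waste)** gives the operational rule: "Plate waste will be estimated as a percentage of food or beverage not consumed in the after eating image". It describes the image pairs as allowing accurate assessment of plate waste. Waste is then classed as compostable, not compostable or unable to determine. The worked example for Figure 6 reads: "this eating occasion will be assessed as four serves of roast beef, and having 30% edible plate waste".
- **Section 2.2 (Study Design)** describes the interview after the four recording days, at which participants clarified image contents with a dietitian and "verified plate waste or if the leftover food or beverage was consumed at a later stage". It then sets the new work: "A secondary analysis by the Accredited Practising Dietitian who was involved in the original analysis of all food images collected during the CHAT study". One objective is to learn whether the five behaviours "can be assessed from image-based food records without interaction with participants".
- **Section 2.3.1 (Ultra-Processed EDNP Foods and Beverages)** shows the rule in use. Two pieces of chicken visible after eating "would not be counted as ultra-processed EDNP serves but rather non-compostable food waste".
- **Section 2.4 (Outcome Variables)** lists percentage of plate waste as an outcome. Section 2.5 names plate waste as an example of environmental impact in the weighting of the Index.
- **Section 3 (Discussion)** describes a prompt asking what became of the leftovers. One of its answers is that the food was kept: "saved for consumption at a later time or other could be incorporated into the mFR application".

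**The concern.** An after-eating image shows what was on the plate when the meal ended. It does not show what became of that food. Section 2.2 recognises this, since the interview asked specifically about it. Section 2.3.5 then defines waste from the image without referring back to the interview.

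At stake is what the waste variable means. Keeping leftovers and eating them later avoids waste. If those leftovers are scored as waste, the variable measures food not finished at one sitting, and the people affected are those who keep their leftovers. Percentage of plate waste is a listed outcome and feeds the Index, so the misclassification would pass into both. The article also says that it gives enough detail for others to reproduce the method, and a second team following section 2.3.5 would have only the image rule to apply.

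**Working it through.** The article gives no statistic that can be recomputed here. The 30% in the Figure 6 example is read from an image that is not shown, so it is taken as stated. The check compares the sections and then works through what the rule implies.

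**Step 1. Does the rule use the interview?**

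- Section 2.3.5 defines waste from the after-eating image alone and gives no exclusion for later consumption.
- Section 2.2 says the interview separated waste from leftovers eaten later.
- No section links the two.
- Three other places point to scoring from the images alone: the objective of doing without participant interaction (2.2), the example that moves food in the after image straight from intake to waste (2.3.1), and the treatment of a saved-food question as a possible future feature (3).

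**Step 2. What happens to one saved leftover under the written rule?**

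| What happened to the leftover | Scored as waste | Scored as intake |
|---|---|---|
| Discarded | yes | no |
| Eaten later within the four days, photographed | yes | yes, at the later occasion |
| Eaten later within the four days, not photographed | yes | no |
| Eaten after the record ended | yes | no (outside the record, so not a missed intake) |

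Only the first row is waste. In the other three the rule adds waste that did not occur. No row understates waste, so the error has one direction.

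**Step 3. How large could it be?**

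Let W be the edible percentage left in the after image and s the share of that leftover eaten later. The article gives no value for s, so every value below is an assumption.

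True waste = W × (1 − s).

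With W = 30% from the Figure 6 example:

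| s (assumed) | True waste | Rule returns |
|---|---|---|
| 0 | 30% × 1 = 30% | 30% |
| 0.25 | 30% × 0.75 = 22.5% | 30% |
| 0.50 | 30% × 0.50 = 15% | 30% |
| 1 | 30% × 0 = 0% | 30% |

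The ratio of scored to true waste is W / [W(1 − s)] = 1/(1 − s), whatever W is:

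- s = 0.10: 1/0.90 = 1.11
- s = 0.25: 1/0.75 = 1.33
- s = 0.40: 1/0.60 = 1.67

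These figures show how the error grows with s. They do not estimate what happened in CHAT.

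**The case against.** The strongest reply is a dilemma. Either the interview answers are used in the scoring and nothing is wrong, or image-only scoring is deliberate because section 2.2 sets out to test whether images suffice without participant contact.

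The first half stands in part. The article nowhere says that the answers are discarded, and the person scoring is a dietitian who took part in the original analysis. A reader might infer that the verification has been thrown away and that the outcome is certainly biased. The article does not support that. It supports only that the written rule leaves the verification out and that no section brings it in.

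The second half also stands in part. The image-only figure is the quantity under test and should not be demoted. But testing whether images suffice needs something to compare them with, and the interview is the only source the article describes on what became of the leftovers. Keeping it out of the plan weakens that objective.

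Four narrower objections are right and limit the point:

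- The three codes in section 2.3.5 classify compostability. They do not record the fate of the food, so the lack of a saved category among them proves little.
- It would be too broad to say that everything left on the plate counts as waste. The Figure 6 example speaks of edible waste, so inedible remains may already be left out.
- A reader might take the Discussion as admitting that images cannot tell binned food from saved food. It makes no such statement and offers the prompt as an enhancement.
- The effect on the Index cannot be stated. The component weights are not yet set, and section 2.5 withholds a high weight from components that images cannot measure accurately.

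**Conclusion.** The point holds as a gap between sections 2.2 and 2.3.5. Followed as written, the rule scores edible leftovers that were saved and eaten as plate waste, and counts them as intake too when the later meal was photographed. The error can only raise waste.

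Its size is unknown. In the article's 30% example, true waste lies between 0% and 30%. The ratios of 1.11 to 1.67 rest on assumed shares of saved food, and a reader should not take them as the expected bias.

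The conclusion assumes that scoring follows section 2.3.5 literally. If the scorer does apply the interview answers, the numbers may be sound, but the stated rule then does not describe what was done and another team could not reproduce it. Either way the text should change. This is a correction worth making before the images are rescored. It does not show that the waste outcome or the Index is invalid.

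**What to change.** In sections 2.3.5 and 2.4:

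1. Define two plate-waste percentages and report them side by side: the image-only percentage as now written, and an interview-verified percentage that excludes leftovers recorded as eaten later.
2. Add a database field for food saved or eaten later, separate from the compostability codes.
3. Use the verified percentage for the waste outcome and the Index component where an interview record exists.
4. Use the agreement between the two percentages to test whether images alone suffice, which answers the objective in section 2.2 directly.
5. Count a leftover that is photographed again as intake once, and only within the record days.

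The cost is one field and the work of retrieving the answers. The main risk is that section 2.2 says that verification took place but does not say that answers were stored item by item. Items without an annotation would have only the image-only figure and should be flagged as undetermined. How many there would be cannot be told from the article, so the number should be reported.
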